**Figure 3 f3:**
[figure not shown]
Anticipated recruitment and enrollment for the nurturing moms study.

### Study instruments

Tracking Form and Demographic Questionnaire: This form consists of two questionnaires to collect demographic information including age, race, and sex. The forms also capture socio-economic information such as employment, education, income, zip code, and other geographical data.Pregnancy Health History or Prenatal Screening Questionnaire: This 3-page questionnaire developed by the American Medical Association can provide useful material to researchers and physicians who want to gather information either prior to pregnancy or during a pregnancy. This form can help determine the risk of a baby having chromosomal conditions or neural tube defects based on the parents’ family history. The form captures past medical history of the father and mother, mother’s history of pregnancies, and exposures during pregnancy (28).Perceived Stress Scale: The perceived stress scale developed in 1983 is a 10-item questionnaire used to gauge stress levels in individuals aged 12 and older. It examines the degree to which situations are perceived as stressful in terms of how unpredictable, uncontrollable, and overloaded respondents find their lives. Score ranges from 0 to 40, with higher scores representing higher levels of stress. Average scores are calculated by adding up the scores and dividing by the number of items, providing a useful indicator for evaluating the overall level of agreement on the likert scale (where 0 = Never, 1 = Almost never, 2 = Sometimes, 3 = Fairly often, and 4 = Very Often) The perceived stress scale has been shown to have a coefficient alpha reliability of.84,.84, and.86 in three studied samples with a test-retest correlation of.85 (29).Everyday Discrimination Scale (Short Form): The everyday discrimination is a five-item instrument measuring experiences of daily discrimination followed by a question about what the person believes was the reason for that daily discrimination. Responses are coded on a 6-point Likert scale ranging from ‘never ‘= 1 to ‘almost everyday’ = 6. Responses are summed across items to produce a score ranging from 10 to 60 (40). The everyday discrimination scale, developed by David Williams in 1997, has shown high levels of internal consistency, convergent validity and divergent validity among African American men and women, and has been widely used in studies of discrimination and health (30, 31).PROMIS^®^ Item Bank v1.0–Sleep Disturbance–Short Form 4a: The PROMIS Sleep Disturbance and Sleep-Related Impairment item banks were developed using a rigorous and systematic methodology, including literature reviews, qualitative item review, focus groups, cognitive interviewing, and psychometric testing. The short form was developed from the full 27-item bank and has been shown to have convergent validity, construct validity, and reliability similar to the full bank. The short form is an 8-item form measuring the quality of sleep and sleep disturbance over the past 7 days. Four items use an intensity scale (not at all, a little bit, somewhat, quite a bit, very much), three items use a frequency scale (never, rarely, sometimes, often, always), and one item (S109) assessing overall sleep quality uses a scale of very poor, poor, fair, good, very good (32).PROMIS^®^ Item Bank v2.0–Emotional Support–Short Form 4a: The PROMIS Emotional Support Short Form was developed by domain experts from the full bank to capture the range of traits and allow researchers to study secondary outcomes without full additional measures. It consists of 4 statements assessing perceived feelings of being cared for and valued as a person. Responses are coded on a 5-point Likert scale ranging from 1 = never to 5 = always. The convergent validity has been supported by strong correlations between the PROMIS Emotional Support short form and measures of similar constructs. Discriminant validity has also been confirmed by negligible correlations between the emotional support measure and measures of dissimilar constructs (33).Maternal Self-Efficacy Questionnaire: The Maternal Self-Efficacy Questionnaire consists of 10 statements assessing mothers’ confidence in their ability to perform parenting-specific tasks such as understanding the baby’s needs and feelings, talking, reading to and playing with the baby, and taking the baby for regular clinic/doctor check-ups. Responses are coded on a 4-point Likert scale (1 = much worse, 2 = somewhat worse, 3 = as good, 4 = better than others). The questionnaire has been found reliable, face and content validity have been shown to be adequate as well as internal consistency and test–retest reliability for the assessment of maternal self-efficacy (34).Pregnancy Experience Scale (PES): The pregnancy experience scale consists of 10 statements measuring how much different aspects of pregnancy have made the mother feel either uplifted and happy or upset and negative. Each response is rated from 0 = not at all to 3 = a great deal. Internal reliability, test-retest reliability, and convergent validity were comparable to the original 41-item PES developed in 2004 (35).Childbirth Experience Questionnaire (CEQ): The childbirth experience questionnaire consists of 22 statements assessing four domains of the childbirth experience; Own capacity, Professional support, Participation, and Perceived safety. It evaluates women’s experience of labor and childbirth, including their perceptions and feelings. For 19 of the items the response format is a 4-point Likert Scale whereas the last three items use a visual analogue scale (VAS). The scoring range is 1 to 4 where higher ratings reflect more positive experiences. The CEQ has demonstrated internal consistency, discriminant validity, equal item-hypothesized scale correlation, and item equal variance (36).Edinburgh Postnatal Depression Scale (EPDS): The Edinburgh Postnatal Depression Scale developed in 1987 remains a prominent tool for measuring postpartum depression. It consists of 10 statements which identify signs and symptoms of depression in the postnatal period. Responses are scored 0, 1, 2, or 3 according to increased severity of the symptom. Items marked with an asterisk (*) are reverse scored (i.e., 3, 2, 1, and 0). The total score is determined by adding together the scores for each of the 10 items. The EPDS demonstrates acceptable sensitivity, specificity and positive predictive value. It has been used in many studies, and has been introduced as a valuable and powerful postnatal depression screening tool in different cultures (37).User Experience Questionnaire: The User Experience Questionnaire consists of 26-items measuring whether people find the using the NurtureVR product to be an overall positive or negative experience. A seven stage scale is used between two opposing descriptors of the user experience. Mothers rate more closely to the descriptor they identify with (38).Virtual Reality Neuroscience Questionnaire (VRNQ): The Virtual Reality Neuroscience Questionnaire consists of 20-item questionnaire measuring the quality of user experience, game mechanics, and in-game assistance, as well as the intensity of the VR induced symptoms and effects. Responses are coded on a 7-point Likert scale, ranging from 1 = extremely low to 7 = extremely high. The higher scores indicate a more positive outcome (39).

#### NurtureVR

The NutureVR mobile app will be installed on the participants’ mobile device. With 49 modules, the program will span five weeks prenatal, optional use during labor, and five weeks postpartum (available for anyone up to six months after childbirth). These modules are aimed to serve as a sanctuary for learning and stress relief, offering education and support for the entire family while fostering intimate connections and bonding to benefit the well-being of the mother and baby. Key features of NurtureVR include education on the effects of stress during pregnancy, 3D VR representations of fetal development, pain management simulations, mindfulness exercises for labor, and postpartum guidance covering topics such as hormonal changes, nutrition, emotional regulation, breastfeeding, and lactation training through VR-enabled practice sessions.

#### Weekly mood state surveys

Once participants have completed baseline surveys, they will have a maternal health and wellness digital intervention (*NurtureVR* headsets) shipped to their homes. The VR box will include a QR code directly linked to mood state surveys via Google Forms. These surveys consist of four rating scales (see below) that subjectively measure participants’ anxiety, mood, pain, and stress levels before and after usage of the VR (see **Figure 4**). Participants will be asked to scan this QR code after each VR session to complete the surveys. They are encouraged to utilize the headsets as often as they wish, but at least once a week.

Anxiety Rating Scale: The anxiety rating scale is a 10-point pictorial Likert scale to measure mother’s feelings of anxiety ranging from 0 = Balanced Mood to 10 = Out-of-control behavior, self-harm (41). Each number corresponds to a face representing the visual level of anxiety. In adults, test-retest reliability of this scale has been used to measure consistency and stability. Analysis using a paired t-test found a significant difference (t(59) = -18.72, *p* <.001) between mean ratings of current and worse pain in the anticipated direction, suggesting that this measure reflects participants’ varying levels of pain (29).Mood Assessment Scale: The mood assessment scale is a 5-item pictorial scale to measure a mother’s overall mood. Each face corresponds to a mood ranging from very sad to very happy. The pictorial mood assessment scale has been shown to have internal consistency and convergent validity in assessing negative affect (42).Pain Scale: The pain scale is a 10-point pictorial Likert scale measuring experience of pain from 0 = no pain to 10 = worst pain. Accompanied by a Visual Pain Analog Scale with 6 pictures of faces corresponding to visual experiences of pain at 0, 2, 4, 6, 8, and 10 of the numerical pain scale. Reliability of the visual pain scale for acute pain measurement as assessed by intraclass correlation coefficients has been shown to be high and sufficiently reliable to assess for acute pain (43).Stress Scale: The stress scale is a 5-item pictorial Likert scale of faces to measure mother’s stress. Each face corresponds to the level of stress ranging from 0 = no distress to 5 = very severe. The stress scale has been shown to have convergent validity in assessing stress and negative affect (42).

**Figure 4 f4:**
[figure not shown]
Weekly mood surveys.

## Discussion

The United States is experiencing a maternal mental health crisis. While maternal mental health conditions can affect individuals of all backgrounds, racial and ethnic minorities experience a higher prevalence of pre-and perinatal mental health conditions (e.g., postpartum depression and anxiety), compared to their White counterparts (7). Although perinatal mental health symptoms are prevalent, these conditions are often stigmatized, which makes it difficult for individuals to seek help. One study found that stigma was the most important barrier to women’s help-seeking process (44), limiting them from accessing much needed support and resources. Virtual reality technology is being used progressively to support the treatment of mental health conditions and has several advantages such as convenience and adaptiveness (45). Virtual reality interventions may be one means of offering feasible, acceptable, and accessible mental health care to mothers, who would otherwise fall through the cracks, due to lack of access, or stigma. The scalability of VR technology could enable public health systems to reach diverse populations by integrating culturally adaptive and accessible interventions into existing healthcare services. By addressing common barriers such as stigma and limited access, VR interventions could be implemented in both urban and rural healthcare settings, offering consistent support to at-risk mothers across communities. Furthermore, VR interventions could be incorporated into public health initiatives aimed at preventive care, promoting early screening and treatment for maternal mental health conditions.

This collaboration with BehaVR/Realized Care aims to shed light on the need for more virtual reality-based interventions that promote mindfulness and education, tailored specifically to perinatal mothers of color. By providing mental health support through VR, health providers can normalize the occurrence of perinatal mental health conditions and empower individuals to overcome the stigma associated with mental health, allowing them to access critical services when needed. Such digital interventions offer a unique opportunity to create immersive and engaging therapeutic environments that can be customized to meet the diverse needs of perinatal mothers.

The use of decentralized and democratized digital technology solutions is crucial in increasing access to care. Virtual reality and other digital platforms can bridge gaps in service delivery, making mental health support more readily available to those who may otherwise be marginalized by traditional healthcare systems. These technologies can deliver consistent, high-quality care regardless of geographical or socioeconomic barriers, ensuring that perinatal mothers receive the support they need. By leveraging these innovative solutions, we can foster a more inclusive and equitable healthcare landscape, ultimately improving outcomes for mothers and their children. From a policy perspective, VR could help alleviate strain on mental health services by offering self-directed, immersive therapies that reduce the need for in-person sessions. Public health agencies could integrate VR tools into maternal health programs within clinics, community centers, and even mobile health units, extending the reach of mental health support to mothers in remote or underserved areas. Policymakers could also establish reimbursement mechanisms and funding for VR-based maternal mental health interventions, making them more affordable and encouraging their widespread adoption.

Decentralized trials are essential for advancing clinical research by making participation more accessible and inclusive. *Nurturing Moms*, as a form of decentralized trial, exemplifies this by allowing perinatal mothers to engage in the study from their homes through virtual reality-based interventions. This approach reduces the burden of travel and time constraints, significantly increasing participation rates among underserved and geographically diverse populations who might otherwise be excluded from traditional trial settings. By leveraging digital technologies and remote monitoring, decentralized trials enhance data collection and real-time monitoring, leading to more comprehensive and accurate data.

This model aligns with the *Health at Home* program, which aims to provide high-quality healthcare to all individuals, regardless of their location. The Nurturing Moms study demonstrates the potential of decentralized trials to deliver consistent, high-quality care, ensuring that perinatal mothers receive the support they need in a convenient and accessible manner. By democratizing access to clinical research and healthcare, decentralized trials like Nurturing Moms promote equity, improve the generalizability of findings, and accelerate the development of new treatments and interventions. Ultimately, this approach fosters a more inclusive and equitable healthcare landscape, proving that decentralized trials and programs like Health at Home are essential for providing good quality healthcare for all.

Our proposed study lays out a thorough plan for implementing a mindfulness-based virtual reality intervention among a group of perinatal women of color, focusing on usability, acceptability, and feasibility. Due to the technological nature of this intervention, we anticipate potential technical challenges with the VR headset and with the web-based application. To enhance understanding and encourage weekly engagement with the Virtual Reality solution, we developed specific strategies tailored to common technological issues as well as troubleshooting documentation. Like all research, our proposed protocol has limitations. First, the sample size of 50 participants limits the generalizability of our findings when applied to a broader population beyond the sample being studied. The sample size of 50 participants, divided evenly between expectant and postpartum mothers, was chosen based on the feasibility goals of this study rather than a traditional power analysis. Given the exploratory nature of this research, the primary aim is to assess the feasibility, acceptability, and initial engagement with the NurtureVR intervention rather than to achieve definitive statistical power for detecting clinical effects. The study focuses on understanding user experiences, the practicality of implementing the intervention in real-world settings, and identifying any barriers to using the VR technology among Black and Latina mothers. This approach allows us to gather valuable qualitative insights and user feedback, which will inform the design of larger, more rigorous studies in the future.

The sample size was chosen with a focus on the feasibility goals of this study, while also considering its potential for generating statistically significant results. We conducted a power calculation using G*Power 3.1 to assess whether our sample size could detect meaningful changes in key outcomes. Specifically, we used a t-test to identify means: difference from a constant (one-sample case), assuming an effect size of 0.5, a power of 95%, and an alpha error probability of 0.05. This analysis yielded degrees of freedom (Df) = 44 and a required total sample size of 45. These results suggest that our planned sample size of 50 participants is sufficient to detect significant findings in this exploratory study. While the primary aim is to assess feasibility and acceptability, this sample size ensures that we have enough statistical power to observe meaningful changes in stress levels and mental health symptoms, providing valuable insights to guide future research and larger-scale trials.

The absence of a control group is another limitation that may impact the internal validity of our findings, as it makes it challenging to attribute observed changes in stress and mental health symptoms solely to the VR intervention. The decision to forgo a control group was influenced by ethical considerations, as we aim to ensure that all participants benefit from the intervention, especially given the known disparities in access to maternal mental health support among Black and Latina mothers. To address this limitation, we plan to explore the use of historical controls from similar populations in previous studies and to conduct a randomized controlled trial (RCT) in the future to better isolate the effects of NurtureVR. This future RCT would allow for more robust comparisons and a deeper understanding of the intervention’s efficacy.

Lastly, while the sample design is inclusive of Black and Latina perinatal women, the exclusion of non-English speakers – given that the Nurture VR modules at this time are only provided in English – may also limit the applicability of our results. This may particularly exclude those who do not speak English as their primary language or those with limited English proficiency, especially among Latina mothers. Future research should aim to replicate this study with a larger sample size and develop new modules that are linguistically tailored to different communities. Despite these limitations, the study’s strengths lie in its ability to reach a wider audience of pregnant and postpartum mothers through an educational and mindfulness virtual reality-based intervention compared to traditional methods.

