#### Participants

Participants in the *Nurturing Moms* study will be recruited through various channels: clinical/health settings, community outreach recruitment events and community organizations, Research Match, and UMiamiHealthResearch.org. Participants will undergo a screening process in which they must meet the following inclusion criteria: 18 years old or older, speaks and understands English, Black or Latina. Additionally, they must be pregnant (less than 36 weeks) or postpartum (up to 12 months after birth). Participants will be disqualified from inclusion in the study based on the following exclusion criteria: a diagnosis of psychosis, inability to speak or understand English, or being neither pregnant (>36 weeks) nor postpartum (up to 12 months). Individuals with a history of seizures, vertigo, significant vision or hearing impairment, significant motion sickness, epilepsy, or sensitivity to flashing light/motion are also excluded from participation. Injuries to the eyes, face, neck, or arms that would make the use of the hardware uncomfortable are also grounds for exclusion. The implementation of these criteria enhances internal validity, optimizing the relevance and reliability of research findings. We aim to enroll 50 participants (25 expectant and 25 postpartum).

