**Figure 2 f2:**
[figure not shown]
Consent process.

During recruitment, all potential participants will be informed about the compensation details. Participants who complete the 5-week intervention will receive $100 as compensation for their time and effort in participating in the research study. This information will be clearly outlined in the consent form and discussed with participants before taking part of the study.

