#### Statistical analysis plan

For the primary objective, General Linear Model procedures will be used to examine effects of Virtual Reality (VR) on stress over time among pregnant and postpartum moms. For the secondary objective, the User Experience Questionnaire and the Virtual Reality Neuroscience Questionnaire will be used to determine feasibility, usability, and acceptability of NurtureVR as an intervention. Measures of central tendency, and frequency distributions will be used for categorical data.

The main dependent measures will be continuous factors: maternal and pregnancy mental health and sleep scores (see **Table 1** for measures). Regression analysis will be used to explore whether sociodemographic factors (e.g., age, income, education), pregnancy factors (maternal experience scale) and postpartum factors (maternal experience scale and childbirth experience questionnaire) are associated with adverse mental and sleep health outcomes. In the statistical analysis, missing data will be handled using multiple imputation techniques to minimize bias and maintain the integrity of the analysis. Outliers will be identified through visual inspections of data distributions and statistical tests, and decisions about their inclusion will be based on their potential impact on the results and the underlying reasons for their occurrence. We will use sensitivity analyses to assess the robustness of findings. Adjustments for multiple comparisons will be made using the Bonferroni correction or false discovery rate (FDR) control to reduce the risk of Type I errors due to the number of outcomes being measured. Covariates such as age, parity (number of previous births), socioeconomic status, and baseline mental health status will be included in regression models to adjust for potential confounding factors and to provide a clearer understanding of the relationships between the intervention and outcomes. Only factors that show significant correlations in preliminary analysis will be entered in the final model. These data are significant as they will be used to generate effect size estimates (and sample sizes) for planned large-scale studies and to build preliminary exploratory models ascertaining factors that predict mental and sleep health outcomes among Black and Latina pregnant and postpartum women.

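### The required size of 45 holds only for an undeclared one-sided test; on the non-directional test of the planned model 95% power needs 54, and 50 complete cases give 93.4%, before any allowance for attrition or multiplicity.

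*Protocol article*

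**What the plan says.** The power calculation is in the Discussion of the protocol article, where the limitations are set out. The test is described thus: "we used a t-test to identify means: difference from a constant (one-sample case"). The inputs are given as "assuming an effect size of 0.5, a power of 95%, and an alpha error probability of 0.05". The result follows: "This analysis yielded degrees of freedom (Df) = 44 and a required total sample size of 45". The text does not say whether the test is one-sided or two-sided.

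The conclusion drawn is "These results suggest that our planned sample size of 50 participants is sufficient to detect significant findings in this exploratory study". The same paragraph goes on to say that the size *ensures* enough power to see meaningful changes in stress and mental health symptoms. The paragraph before it says that the number "was chosen based on the feasibility goals of this study rather than a traditional power analysis".

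Elsewhere in the article:

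- **Participants:** "We aim to enroll 50 participants (25 expectant and 25 postpartum").
- **Statistical analysis plan:** General Linear Model procedures are planned for stress over time, with no one-sided test declared. Missing data are to be multiply imputed. On multiplicity: "Adjustments for multiple comparisons will be made using the Bonferroni correction or false discovery rate (FDR) control".
- **Timeline:** the surveys are repeated three months after the programme ends. No attrition rate is given.

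**The concern.** A reader takes alpha 0.05 with no further remark to be two-sided, and a General Linear Model effect of time is tested with a non-directional F-test. On that reading 45 is too small for 95% power, and so is 50. The calculation also uses unadjusted alpha and counts every enrolled woman as a completer. The same article plans a multiplicity correction and places the post-programme survey three months after the last week of use.

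What is at stake is how far the stated assurance can be trusted. The article says these data will supply effect sizes and sample sizes for larger studies. An optimistic calculation that hides its one-sided assumption could be carried into that planning.

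**Working it through.** **Inputs.** Standardised effect d = 0.5, alpha = 0.05, target power 95%, one-sample t-test on the pre-post change (all from the Discussion); planned N = 50 (Participants). Sidedness is not stated, so both versions were tried.

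**Formula.** For n complete pairs, df = n − 1 and the noncentrality is d√n. One-sided power is the probability that a noncentral t exceeds the critical value t(1 − α, df). Two-sided power uses t(1 − α/2, df) and adds the negligible lower tail. The required n is the smallest that reaches 0.95.

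**Step 1: reproduce the stated figure (one-sided).**
- n = 44: power 94.7%.
- n = 45: df = 44, noncentrality 0.5 × √45 = 3.354, critical value 1.680, power 95.1%.

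The one-sided requirement is therefore 45 with df 44, exactly as printed. At n = 50 the one-sided power is 96.7%.

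**Step 2: the same inputs, two-sided.**
- n = 53: power 94.7% (0.9465).
- n = 54: noncentrality 0.5 × √54 = 3.674, critical value 2.006, power 95.0%.
- n = 50: noncentrality 0.5 × √50 = 3.536, critical value 2.010, power 93.4%.

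The two-sided requirement is 54, which is 4 more than planned. The shortfall in power at 50 is 95.0 − 93.4 = 1.6 points.

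**Step 3: check against the planned model.** The F-test of a time effect with 1 numerator df, using a noncentral F with noncentrality n·d², also needs n = 54. This holds with n − 1 error df and with n − 2 (two cohorts in the model). Power at 50 is 93.4% in both.

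**Step 4: what 50 complete cases can detect.** Solving the two-sided formula for d at n = 50 gives 0.40 at 80% power and 0.52 at 95% power.

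**Step 5: the two omitted allowances, as labelled assumptions.** The article gives no attrition rate and no number of tests, so these are illustrations. All are two-sided at d = 0.5, on complete cases; Bonferroni uses 0.05/m.

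| Completers | No adjustment | Bonferroni, 2 tests | Bonferroni, 4 tests |
|---|---|---|---|
| 50 (no loss) | 93% | 89% | 82% |
| 45 (10% loss: 50 × 0.9) | 91% | 85% | 77% |
| 40 (20% loss: 50 × 0.8) | 87% | 79% | 70% |

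Four is the number of instruments that Table 2 repeats at three months (stress, sleep disturbance, emotional support, self-efficacy). It is one possible count, not one that the article fixes.

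**The case against.** The strongest reply is that nothing was miscalculated. The figure of 45 with df 44 is exact for the named test run one-sided, and the objective, to reduce stress, is directional. That stands: had a one-sided 0.05 test been declared, 45 would be right. But none is declared, and the planned model does not supply one.

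A second reply is that the gap is small and the study calls itself exploratory. This also stands in part. A reader might infer that the trial is badly underpowered. The documents do not support that: two-sided unadjusted power is 93.4% at 50 and still 91% at 45. The lower figures in the table rest on assumed losses and assumed test counts. FDR control, named as the alternative to Bonferroni, would usually cost less power, and multiple imputation may recover some of what attrition takes away.

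Two further strong readings should be resisted. A reader might work out power for each cohort of 25 separately, but the article states no cohort-specific test. A reader might also see a flat contradiction between choosing N without a traditional power analysis and then reporting one. The two paragraphs can largely be read together: N was set for feasibility, and the calculation was a check on it. What does not fit that reading is the word *ensures*.

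**Conclusion.** The point holds in a limited form. The printed requirement of 45 depends on an undeclared one-sided test and does not match the planned General Linear Model, whose non-directional test needs 54 for 95% power. With 50 complete cases the power is 93.4%. That the planned test is two-sided is an inference from the model named and from the absence of any declared one-sided test; the article does not say so outright.

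Sidedness alone costs 1.6 points and would not change any practical decision. The more important weakness is that the assurance of sufficient power ignores the multiplicity adjustment and the three-month follow-up that the article itself plans. The direction of both effects is clear. Their size is not, because it depends on a test count and an attrition rate that the article does not give.

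**What to change.** Revise the power paragraph in the Discussion, with no change to enrolment:

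1. State two-sided alpha 0.05 and a paired change. Give 93% power at a standardised change of 0.5 with 50 completers, and a detectable standardised change of 0.40 at 80% power.
2. Say plainly that attrition and multiplicity are not included. If their effect is shown, label it as assumed: for example 91% with 45 completers and 87% with 40; at 50 completers, 89% with Bonferroni over two tests and 82% over four; 70% with four tests and 40 completers. Note that FDR control and multiple imputation may cost less.
3. Replace the statements that 50 is sufficient and that the size ensures enough power with wording that matches these figures.
4. Align with the preceding paragraph by saying that N was chosen for feasibility and that the calculation is a check on it.

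The cost is wording only, and a slightly less favourable stated power.
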